### Primary outcome

The primary outcome is overall mental state as measured using the PANSS total score. PANSS subscale scores for positive, negative and general scales will also be reported.

### Secondary outcomes

Secondary outcomes are: the PSYRATS subscales (preoccupation, conviction, distress, and disruption to life) adjusting for the presence and frequency of symptoms; the SFS; and service utilisation.

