As with CBT, ACT does not aim to eliminate psychotic symptoms, but to reduce resultant distress and disability to enable better quality of life. Both hallucinations and delusions appear to be multidimensional phenomena, in which different dimensions may show significant variation between individuals and over time, e.g., frequency, degree of preoccupation and degree of conviction in content, as well as resultant distress and impact upon behavior [40,41]. The dimensions of preoccupation and conviction appear particularly important in determining levels of disability and subjective distress. Indeed, in the general population, beliefs with the same themes as delusions may be held in attenuated form without interfering with social functioning or being found significantly distressing [42,43]. The dimensions of preoccupation and conviction appear more important than content itself in distinguishing patients with schizophrenia from non-patients who hold unconventional beliefs [42,43]. The cognitive defusion techniques used in the Acceptance component of ACT provide an avenue for reducing the level of preoccupation and conviction with psychotic symptoms, but, in contrast to CBT, without requiring modification of the content of beliefs themselves. The ACT model proposes that preoccupation with distressing internal experiences such as psychotic symptoms is maintained by the paradoxical effect of repeatedly engaging in unsuccessful attempts to avoid and suppress them [29,30]. The Acceptance component of ACT involves exercises to help the person recognise the futility of trying to directly suppress and control such experiences, combined with teaching skills in mindful observation of experiences in a detached manner without attempting to change or judge them. The use of defusion techniques is associated with increased tolerance of experimentally induced pain, as opposed to distraction or no instruction [32], suggesting that this is applicable to aversive internal experiences in general. In addition, there is evidence that defusion techniques are particularly effective in reducing repetitive cognitive processes such as depressive rumination, anxious worry and persistence of obsessive thoughts (e.g., [32,44]). These findings suggest that such techniques may also be helpful for reducing preoccupation with distressing delusions [45]. Further, there is a strong argument that distancing and acceptance techniques may also be specifically applicable to preoccupation with auditory hallucinations given their ‘verbal’ form, their compelling salience, and the propensity of voice hearers to be drawn into reacting to the literal content [46,47]. In support of this contention, several strands of research have found acceptance strategies to be helpful in managing voices (see [39] for review).

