The Commitment component of ACT involves exercises to help the patient clarify their personal values and encouraging commitment to take action in line with these values. It is expected that this will lead to adaptive behavioral change, reducing the impact of negative symptoms and improve social functioning. It might be noted that White et al. [50] found a reduction in negative symptoms in a feasibility trial of ACT for emotional dysfunction following psychosis. However, the very small sample size and apparent baseline differences makes it difficult to draw strong conclusions from this finding.Figure 1 summarises the expected pathways of action for ACT. Acceptance and defusion processes are expected to lead to reduced preoccupation, conviction, distress and disruption to life associated with hallucinations and/or delusions resulting in a general improvement in positive symptoms. Increased commitment to valued action is expected to lead to adaptive behavioral change and a general improvement in negative symptoms. The net outcome of these changes will be observed in improvements in overall mental state and social functioning.

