##### Positive symptoms

The Psychotic Symptom Rating Scales (PSYRATS - [41]) is a semi-structured interview designed to assess the severity of an individual’s auditory hallucinations and delusions across a range of physical and psychological dimensions. We use items from the PSYRATS to assess the severity of hallucinations and delusions according to the specific dimensions of interest to the study which include preoccupation, conviction, distress and disruption to life. In order to be able to control for the presence and frequency of symptoms, the frequency dimension of the PSYRATS auditory hallucinations subscale and the amount of preoccupation dimension of the PSYRATS delusions subscale is also be assessed. This scale has good psychometric properties and excellent inter-rater reliability across both scales is excellent, ranging from 0.788-1.00 for hallucinations and 0.884 – 1.00 for delusions [41].

Delusions are further assessed using the Peters Delusions Inventory (PDI - [43]). This self-report measure assesses delusional thinking more broadly and has been found to be a reliable and valid of delusional thinking in the general population and to discriminate between clinical and non-clinical samples on conviction, preoccupation and distress [43]. Participants are asked to indicate the presence or absence of 21 delusional beliefs (e.g., “Do you ever feel as if people are reading your mind?”) giving a total score of 0–21. Each delusional belief endorsed is then rated on dimensions of preoccupation, conviction and distress. The total number of items endorsed on the PDI will be used to assess for any paradoxical increases in symptom reporting.

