### Procedure

Assessments are conducted by research assistants trained in administration of the measures at baseline (prior to randomisation), at the end of therapy approximately three months following baseline (endpoint), and at six months following the end of therapy (follow-up). Outcome measures, process measures and medication are assessed at all three time points except for service utilisation which is administered only at baseline and follow-up. Cognitive measures are done where possible at Time 1 or, if necessary, at a later time point.

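### PSYRATS delusion outcomes are adjusted for amount of preoccupation, which is itself an outcome and an ACT target; with concurrent values this removes part of the effect under test

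*Protocol article*

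**What the plan says.** The Secondary outcomes section of the protocol article lists "the PSYRATS subscales (preoccupation, conviction, distress, and disruption to life) adjusting for the presence and frequency of symptoms". The Positive symptoms section names the control variables and their purpose: "In order to be able to control for the presence and frequency of symptoms", it says, "the frequency dimension of the PSYRATS auditory hallucinations subscale and the amount of preoccupation dimension of the PSYRATS delusions subscale is also be assessed". The same section describes the outcomes as "the specific dimensions of interest to the study which include preoccupation, conviction, distress and disruption to life", so preoccupation appears in both roles.

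The section on aims and mechanisms makes preoccupation something that treatment should change: "Acceptance and defusion processes are expected to lead to reduced preoccupation, conviction, distress and disruption to life associated with hallucinations and/or delusions". It also treats preoccupation and conviction as important in determining disability and subjective distress.

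On timing, the Procedure section states "Outcome measures, process measures and medication are assessed at all three time points except for service utilisation". Nothing in the article says whether the adjustment uses the baseline value or the value from the same visit as the outcome.

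**The concern.** A covariate is safe in a randomised comparison if treatment cannot have altered it. Here the delusion control is a dimension that ACT is designed to lower and that the trial's own model places upstream of distress and disruption. Comparing the arms at equal post-treatment preoccupation takes out the part of the benefit that runs through preoccupation. If the preoccupation outcome is built from the same item, it is compared with itself.

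At stake is hypothesis (b), on preoccupation, conviction, distress and disruption to life. It bears directly on the stated purpose of reducing distress and disability. A null result for delusions would be hard to interpret: it could mean that ACT did nothing, or that its effect had been held constant by the adjustment.

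The hallucination control, the frequency item, is a different case. The article expects ACT to leave frequency unchanged, so conditioning on it should remove nothing. It also reports that, in one earlier trial, ACT patients were less likely to say their symptoms had fully remitted, and hypothesis (h) provides for a paradoxical rise in reporting. If such a rise reached the PSYRATS reports, adjustment would bias the result in favour of ACT.

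**Working it through.** **Which visit's value?** Three features point to concurrent values. The control items are described among the outcome measures, which are taken at baseline, endpoint and follow-up. The Covariates section (premorbid IQ, abstract verbal reasoning, verbal memory, antipsychotic medication) omits them. The Statistical analysis section treats baseline as one of the repeated occasions. This is an inference; no time point is stated.

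**The plan's own figure.** The Sample size section gives 53 per arm for d = 0.55, 80% power and α = 0.05. A two-sided two-sample t-test needs 52.87, rounded up to 53, and 53 per arm gives 80.1% power (normal approximation: 52 per arm, and 80.8% power at 53). The figure reproduces. It concerns the PANSS total and serves here only as a scale.

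**Inputs.** From the article: n = 53 per arm and 0.55 SD, borrowed from the PANSS because no PSYRATS effect is given. Assumed, because the article gives no values: within-arm correlation ρ between control and outcome of 0.3 to 0.8, and an ACT effect on the control, d_F, of 0.55, 0.3, 0.2 or 0 SD reduction, or a 0.2 SD increase (d_F = −0.2).

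**Formulas.** Positive values mean improvement.
- Adjusted effect = d_Y − ρ × d_F.
- Residual SD = √(1 − ρ²). The variance of the treatment coefficient is inflated by 1 + d_F²/4.
- Power = Φ[adjusted effect / (√(1 − ρ²) × √(1 + d_F²/4)) × √(53/2) − 1.96].

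Example with d_F = 0.55 and ρ = 0.5: 0.55 − 0.5 × 0.55 = 0.275. Then 0.275 / (0.866 × 1.037) = 0.306; 0.306 × 5.148 = 1.576; Φ(1.576 − 1.96) = 35%.

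**Results:** adjusted effect in SD (share of 0.55 kept; power).

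| ACT effect on control | ρ = 0.3 | ρ = 0.5 | ρ = 0.7 | ρ = 0.8 |
|---|---|---|---|---|
| 0.55 lower | 0.385 (70%; 52%) | 0.275 (50%; 35%) | 0.165 (30%; 21%) | 0.11 (20%; 15%) |
| 0.3 lower | 0.46 (84%; 69%) | 0.40 (73%; 65%) | 0.34 (62%; 68%) | 0.31 (56%; 75%) |
| 0.2 lower | 0.49 (89%; 75%) | 0.45 (82%; 76%) | 0.41 (75%; 84%) | 0.39 (71%; 91%) |
| none | 0.55 (100%; 84%) | 0.55 (100%; 90%) | 0.55 (100%; 98%) | 0.55 (100%; >99%) |
| 0.2 higher | 0.61 (111%; 91%) | 0.65 (118%; 97%) | 0.69 (125%; >99%) | 0.71 (129%; >99%) |

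In the 0.2 and 0.3 rows power holds up better than the effect does, because the covariate also reduces residual variance. The harm there is mainly a biased estimate.

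**Same item as outcome and control.** At one visit ρ = 1 and d_F = d_Y, so the adjusted effect is 0.55 − 1 × 0.55 = 0.

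**Simulation check** (3,000 trials per scenario, d_F = 0.55). Concurrent adjustment gave 0.268 (power 33%) at ρ = 0.5 and 0.166 (21%) at ρ = 0.7. Adjustment for the baseline value, with an assumed baseline-to-post correlation of 0.6, gave 0.543 (82%) and 0.550 (86%).

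The calculation uses a single post-treatment visit. It simplifies the planned mixed model but shows the direction and rough size of the bias.

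**The case against.** The strongest reply is about timing. The items are also measured at baseline, the Statistical analysis section names no time-varying covariate, and baseline adjustment would be harmless. A reader might infer that the article states post-randomisation adjustment; it does not. This part of the reply stands, and the bias is therefore conditional. Baseline values would remove the bias in conviction, distress and disruption. They would still sit awkwardly with the preoccupation outcome: if the item is shared, its baseline value is already in the model as a response.

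A reader might also extend the delusion problem to hallucinations. The article does not support that. It expects no effect on frequency, reports none in two earlier ACT trials, and assigns the test of paradoxical reporting to the number of PDI items endorsed. Bias there needs a shift in reported PSYRATS presence or frequency, which the article leaves open but does not predict.

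Nor is it established that preoccupation is adjusted for itself, since the items forming that outcome are not listed.

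The adjustment also has a rationale. The article suggests that control patients may deny symptoms more often. If denial also lowers rated distress, which is an assumption, an unadjusted contrast could be biased against ACT. That is a reason to keep a conditional analysis as a supplement, though not to make it the main one.

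Finally, only secondary outcomes are touched. PDI dimensions, the Sheehan Disability Scale, the Social Functioning Scale and the PANSS positive scale carry no such adjustment.

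**Conclusion.** The concern holds for the delusion outcomes, conditionally on timing. The article fixes as control a variable that it also names as an outcome, a treatment target and a determinant of other outcomes. With concurrent values, the loss is 11–44% of a 0.55 SD effect if ACT lowers the control by 0.2–0.3 SD, and 30–80% if it lowers it by 0.55 SD, where power falls from about 80% to between 52% and 15%. These figures rest on assumed correlations of 0.3–0.8 and assumed effects on the control. A flat statement that most of the effect would vanish describes only the upper part of that range.

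For hallucinations there is no bias if the article's expectation on frequency is right. If ACT raised the reported control by 0.2 SD, a true effect of 0.55 SD would be overstated by 11–29%.

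The primary outcome and the sample size are unaffected. This should be fixed, but it does not threaten the main result of the trial.

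**What to change.** In the Secondary outcomes and Positive symptoms sections, and in the analysis plan to match:
- Make the main PSYRATS treatment contrast unadjusted, or adjusted for baseline values only, and say which.
- Do not use amount of preoccupation as a control for any delusion outcome.
- Report any analysis conditional on concurrent presence or frequency as exploratory, labelled as conditioning on a post-randomisation variable, beside the main result.

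The change is to wording only and needs no new data. Its price is that the main contrast no longer corrects for differential denial of symptoms between arms; the exploratory analysis can still examine that.

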### Procedure

Assessments are conducted by research assistants trained in administration of the measures at baseline (prior to randomisation), at the end of therapy approximately three months following baseline (endpoint), and at six months following the end of therapy (follow-up). Outcome measures, process measures and medication are assessed at all three time points except for service utilisation which is administered only at baseline and follow-up. Cognitive measures are done where possible at Time 1 or, if necessary, at a later time point.

### Blindness

Considerable efforts are made to ensure that the blindness of raters is maintained. Offices, data storage and travel logs of raters and therapists are kept separate. Participants and clinical staff are regularly reminded not to divulge details of their therapy to the raters and a reminder sign placed prominently in front of the participant during assessments. Blindness is assessed after endpoint and follow-up assessments by asking raters classify participants into treatment condition and to indicate their level of confidence. Breaches in blindness are recorded and addressed by changing the rater wherever possible.

### Statistical analysis

The primary focus of the analysis is differential changes in the ACT group versus Befriending from baseline to endpoint, which will be analysed within the framework of Treatment Group (ACT vs. Befriending) by Measurement Occasion (baseline, endpoint, follow-up) design. Analyses will be undertaken using mixed-model repeated measures (MMRM) which is the recommended method for examining clinical trial data [75]. Primary evidence of the efficacy of ACT will be a significant two-way interaction demonstrating greater change in outcome measures in the ACT group from pre- to post-therapy. Baseline to follow-up interactions with treatment group will also be examined. Where there are significant group x time interactions, planned contrasts will compare changes from baseline under each intervention at endpoint and follow-up.

Intention-to-treat (ITT) analysis [76] will be used. MMRM is well-suited to ITT analyses because this approach uses all available information from subjects as randomised to produce ITT estimates of treatment effects under only mild assumptions concerning the nature of withdrawal [75]. Most importantly, subjects with incomplete data are not discarded and missing data are not replaced with unprincipled estimated values or observations carried forward [77]. This approach is regarded as the most appropriate method of analysing RCT data by the highest quality journals, which have adopted the CONSORT standard (see, e.g., [78]). However, if data are grossly non-normal and cannot be successfully transformed, non-parametric methods will be used.

The mediational impact of pre to post AAQ, RSQ and medication dose change will be assessed using the Sobel test [79], arguably the most powerful current method of detecting indirect effects [80]. This test assesses the statistical significance of the product of the coefficients for treatment-mediator and mediator-outcome effects. A bootstrapped multivariate extension of the Sobel test described by Preacher and Hayes [81,82] will be used, which is suitable for non-parametric data, and allows us to examine both the total indirect effect and the individual effect of each specified mediator, controlling for the other.

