#### Sample size

We determined that a sample of 53 participants per treatment arm would enable endpoint between group effects for overall mental state of *d =* 0.55 or greater to be detected with 80% power (α = 0.05). The effect size chosen is a little lower than the *d = 0.60* reported in the TORCH [38] and Gaudiano and Herbert [36] trials for overall mental state.

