#### Recruitment and randomisation

Participants are recruited from public mental health services and private providers including non-government psychiatric disability rehabilitation services in metropolitan Melbourne, Australia. Potential participants are identified via clinician referral, supplemented by review of clinician case lists and advertising within services and print media to generate self-referrals. Participants who provide written informed consent undertake an interview to complete the baseline assessment measures prior to randomisation and confirm eligibility.

The randomisation materials and procedure was prepared at study inception by an independent statistician who subsequently had no further involvement in the project. Randomisation is stratified by site of recruitment (9 sites) and recovery style (integration or sealing over). Within each of the 18 factorial combinations of site of recruitment and recovery style, a random permuted blocks procedure was used to generate a list of As and Bs. The procedure was implemented in Microsoft Excel, and a high quality random number generator was used to choose each random sequence of blocks, without replacement within each sequence. For each of the 18 groups a numbered pile of sealed opaque envelopes was prepared, each envelope containing a slip of paper marked ‘A (ACT)’ or ‘B’ (Befriending), in accord with the generated sequence. The printing on the slips is very faint, and slips were folded so that no hint of the A or B can be seen through the envelope even when held up to light. Using the envelopes in numbered order, for the appropriate group, gives an allocation of subjects to treatment A or B in accordance with CONSORT guidelines. The random number seed, and the 18 printed sequences of As and Bs, are sealed in double envelopes, with again, no hint of the contents being visible through the envelopes. Assignment of participants to conditions using these materials is undertaken by a research assistant who works independently of staff involved in the recruitment, assessment and management of participants in the study. Group allocation is revealed to the trial therapists and by letter to the participant and their primary treating clinician.

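### The primary PANSS contrast is a difference in raw change from a pre-randomisation baseline; giving the arms a common baseline mean would make it more precise at no cost in data

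*Protocol article*

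**What the plan says.** All references are to the protocol article.

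- **Primary outcome:** "The primary outcome is overall mental state as measured using the PANSS total score".
- **Statistical analysis:** the outcome is to be "analysed within the framework of Treatment Group (ACT vs. Befriending) by Measurement Occasion (baseline, endpoint, follow-up) design", using mixed-model repeated measures. Baseline is therefore one of three levels of the occasion factor and part of the response. Primary evidence of efficacy is the two-way interaction from before to after therapy, that is, greater change under ACT. The section mentions neither a baseline PANSS covariate nor equal baseline means across arms.
- **Sample size:** the trial is sized at 53 per arm, which "would enable endpoint between group effects for overall mental state" to be found at a standardised difference of 0.55, given power of 80% and a 5% significance level. The section gives no baseline–endpoint correlation.
- **Procedure:** baseline assessments are made before randomisation.
- **Covariates:** the measures listed are premorbid IQ, abstract verbal reasoning, verbal memory and antipsychotic medication. Baseline PANSS is not among them.

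**The concern.** Because baseline precedes randomisation, the two arms have the same expected baseline PANSS, and any observed difference is chance. A model that gives each arm its own baseline mean ignores this. Its baseline-to-endpoint interaction subtracts the whole chance baseline difference from the endpoint difference. The efficient correction subtracts only the part that baseline predicts. Subtracting all of it adds noise.

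The precision of the primary estimate is at stake. There is also a link to the sample size, which was worked out for a between-group difference at endpoint, while the test is a difference in change. The two have the same power only at one value of the correlation, and the article does not give that correlation.

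**Working it through.** **Inputs from the article (Sample size):** 53 per arm, d = 0.55 at endpoint, 80% power, α = 0.05. Sidedness is not stated.

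**Inputs assumed:** the baseline–endpoint correlation r of PANSS total, shown over a range; equal SDs at baseline and endpoint (relaxed in step 5); complete data (relaxed in step 4).

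**1. Reproduce the stated sample size.** For a two-sided two-sample t-test with 53 per arm, df = 104 and the noncentrality is 0.55 × √(53/2) = 2.83. Power is 80.1%; with 52 per arm it is 79.3%. So 53 reproduces as a two-sided, endpoint-only comparison. The normal approximation gives 52. A one-sided test would need 41 and does not reproduce.

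**2. Variance of the two contrasts.** Set the variance of the endpoint-only comparison to 1.

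- Planned (free baseline means, difference in change): 2(1−r).
- Baseline-adjusted, or common baseline mean: 1−r².
- Share of variance saved: 1 − (1−r²)/[2(1−r)] = 1 − (1+r)/2 = (1−r)/2.

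A generalised least squares calculation with three occasions and a compound-symmetric correlation, with baseline means free and then constrained equal, gives the same savings: 30% at r = 0.4 and 15% at r = 0.7.

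**3. Power with 53 per arm.** Noncentral t, with effective d = 0.55/√[2(1−r)] as planned and 0.55/√(1−r²) adjusted.

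| r (assumed) | 2(1−r) | 1−r² | Saving | Effective d, planned → adjusted | Power, planned → adjusted |
|---|---|---|---|---|---|
| 0.4 | 1.20 | 0.84 | 30% | 0.502 → 0.600 | 72.6% → 86.4% |
| 0.5 | 1.00 | 0.75 | 25% | 0.550 → 0.635 | 80.1% → 90.0% |
| 0.6 | 0.80 | 0.64 | 20% | 0.615 → 0.688 | 88.0% → 93.9% |
| 0.7 | 0.60 | 0.51 | 15% | 0.710 → 0.770 | 95.2% → 97.5% |

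Over r = 0.2 to 0.9 the saving runs from 40% to 5%. The planned contrast equals the endpoint-only comparison when 2(1−r) = 1, that is at r = 0.5. Below that it is weaker, and above it is stronger. The adjusted variance 1−r² is never above 1.

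**4. Missing data.** The article states no dropout rate. Assume 10% have baseline only and a further 10% miss follow-up only. The relative variances become 1.293 against 0.933 at r = 0.4 (saving 28%) and 0.657 against 0.567 at r = 0.7 (saving 14%). The conclusion does not change.

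**5. Unequal SDs.** If the baseline SD is k times the endpoint SD, the planned variance is 1 + k² − 2rk and the adjusted variance is still 1−r². The difference is (k−r)², which is never negative. With k = 0.8 the saving is 16% at r = 0.4 (1.00 against 0.84) and 2% at r = 0.7 (0.52 against 0.51).

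**The case against.** The strongest reply is that nothing here is an error. The planned contrast is unbiased under randomisation, keeps its Type I error, and answers the article's stated question about differential change. This stands: the loss is of efficiency, not validity.

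A second reply is that the power shortfall needs r below 0.5. Eligibility requires symptoms present continuously for six months and no antipsychotic change in the previous eight weeks, and endpoint falls about three months after baseline. That suggests, without proving, a fairly stable score. This also stands in part. A reader might infer that the trial is underpowered or that 53 per arm is wrong, but the article does not support that: at r = 0.5 the planned contrast has the stated power, and above 0.5 it has more.

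A third reply is that using baseline as a covariate would normally drop participants with no post-baseline PANSS, against the article's commitment to keep incomplete cases. This is fair against the covariate version only. With baseline kept as a response and its mean shared across arms, those participants remain in the model.

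A reader might also infer that the model wrongly leaves out the randomisation factors, since "Randomisation is stratified by site of recruitment (9 sites) and recovery style (integration or sealing over") and neither factor appears under Statistical analysis. The documents do not support that reading. The article neither includes nor excludes these terms, and a condensed article may leave them to the full analysis plan. A site or recovery-style effect that is constant over time also cancels from a baseline-to-endpoint interaction, so a loss of precision from that source is not shown.

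**Conclusion.** The point holds as a matter of efficiency. The article names baseline as a response occasion and a difference in change as the primary test, so this is a stated choice rather than a detail left open, and a method with no larger variance is available from data already collected. The exact saving cannot be read from the documents: 15% to 30% is not a property of this trial but follows from an assumed r of 0.4 to 0.7 with equal SDs and complete data. What does not depend on the value of r is the direction: under the model in the working, adjustment never increases the variance, and power then stays at or above that of the endpoint comparison used for sizing, whatever r is, apart from a trivial cost in degrees of freedom. The change is recommended, but the planned analysis would not be invalid without it.

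**What to change.** In the Statistical analysis section, keep the mixed model with baseline, endpoint and follow-up as responses, but state that the two arms share a common baseline mean, so that group effects enter only at endpoint and follow-up. Name the ACT minus Befriending difference in PANSS total at endpoint, taken from this model, as the primary estimate and test.

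The cost is a change of wording. It needs no new data, does not alter the sample size or the intention-to-treat principle, and keeps participants with incomplete data.
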